### Sample size

The sample size of 32 (*n*=16 per arm), calculated using SigmaPlot v. 14.0, was based on a difference of 2.5 min between groups and standard deviation of 2.0 min in time to exhaustion during endurance treadmill testing at the final visit, as reported previously by Huang et al. [12, 13]. Using a two-sided sample *t*-test with a significance level of 0.05, it was calculated that a study with 24 participants, 12 per arm would have an 80% power to detect the assumed difference between the intervention groups. To adjust for an assumed dropout rate of 20% the total sample size would be 30. To evenly stratify the participants by sex in even blocks, two additional participants were added, bringing the total sample size to 32. This would provide for an effect size of 0.8, which is deemed a large effect.

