**Methods:**

This 9-week randomized, placebo-controlled, double-blind, parallel trial will assess the ergogenic effects of a probiotic (5 billion colony-forming units/day, for 6 weeks) in healthy, non-elite runners (*N*=32; 18–45 years). Participants will be monitored via daily and weekly questionnaires during the 2-week pre-baseline, 6-week intervention, and 1-week washout. Questionnaires will inquire about activity, muscle soreness, gastrointestinal symptoms, cold and flu symptoms, stool form and frequency, and adverse events. During the pre-baseline visit, maximal oxygen uptake (V̇O_2_ max) is assessed to set appropriate individualized workload settings for the treadmill time-to-exhaustion endurance tests. These time-to-exhaustion endurance running tests will be completed at an intensity of 85% VO_2_max at baseline and final visits. During these tests, self-perceived exercise effort will be rated via the Borg Rating of Perceived Exertion scale and finger sticks assessing capillary blood glucose and lactate concentrations will be collected every 3 min. Additional questionnaires will assess diet and motivation to exercise. Body composition will be assessed using air displacement plethysmography at the baseline and final visits. Hypotheses will be tested using two-sided tests, and a linear model and with a type I error rate of *α*=0.05. Primary and secondary outcomes will be tested by comparing results between the intervention groups, adjusting for baseline values.

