
Recent studies suggest that probiotics, namely *Lactobacillus*, could improve athletic performance. These ergogenic effects were detected in athletes with various sport specializations, including runners [7, 8, 12–15]. Huang et al. observed a dose-dependent improvement in time-to-exhaustion during treadmill testing in non-elite athletes (*N*=54, age 20–30 years) who received a *Lactobacillus* probiotic (30 billion CFU and 90 billion CFU) for 6 weeks [12, 13]. Similarly, time-to-exhaustion was improved in a running protocol after administering a probiotic formulation composed of *Lactobacillus*, *Bifidobacterium*, and *Streptococcus* to male non-elite runners (*N*=10, age 25–29 years) for 4 weeks [8]. Possible endurance-enhancing mechanisms include alteration of the gut microbiota which could impact muscle substrate use, increased glucose availability and enhanced antioxidant defense to combat exercise-induced oxidative stress [13]. In contrast, in elite athletes, there was no improvement in running endurance after a 14-week *Lactobacillus* intervention (*N*=50, age 20–25 years) compared to placebo [11].

Interpretation of the performance findings related to probiotics may be clouded by variations in training status of runners enrolled in the research. Some elite athletes who routinely train and perform at intensities near maximum V̇O_2_ max value may experience less ergogenic effect on time-to-exhaustion with probiotics compared to non-elite athletes [11, 16]. Probiotic administration in the non-elite athlete may produce greater effects on physiological responses to exercise such as endurance, perception of muscle effort, and energy metabolism (blood lactate and blood glucose). Non-elite runners may also benefit from probiotic-induced immunomodulatory and gastrointestinal effects that could modulate performance, but this has yet to be determined [17].

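### The sample-size section credits 32 participants with an effect size of 0.8, but its own inputs give 1.25, and its stated t-test does not reach 80% power at 0.8

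*Protocol article*

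**What the plan says.** The Sample size section of the protocol article states its inputs in full. The calculation "was based on a difference of 2.5 min between groups and standard deviation of 2.0 min in time to exhaustion", taken at the final visit and attributed to earlier published work. The method is given as: "Using a two-sided sample *t*-test with a significance level of 0.05". The result is that "a study with 24 participants, 12 per arm would have an 80% power to detect the assumed difference between the intervention groups". A 20% dropout allowance takes 24 to 30, and two more participants are added so that the sex-stratified blocks come out even, making 32 (16 per arm). The paragraph then ends: "This would provide for an effect size of 0.8, which is deemed a large effect".

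The section gives no second difference, SD, power level or baseline correlation that could lead to 0.8. Separately, the Statistical methods section and the Primary and secondary outcomes section specify a primary comparison adjusted for baseline time to exhaustion. The sample-size calculation does not use that adjustment.

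**The concern.** The closing sentence describes the sensitivity of the primary comparison, and it disagrees with the figures a few lines above it. An effect size attached to a sample size can mean the effect assumed for planning or the smallest effect detectable at the planned power. On either meaning, 0.8 should follow from the stated difference, SD, test and number per arm.

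If it does not, a reader is told that the trial covers a difference of 0.8 × 2.0 = 1.6 min when the calculation was made for 2.5 min. A non-significant result could then be taken as evidence against an effect of 0.8 SD, although the power stated in the section was never calculated for that effect.

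**Working it through.** **Inputs, all from the Sample size section.** Difference 2.5 min; SD 2.0 min; two-sided two-sample t-test; alpha 0.05; target power 80%; dropout 20%. Allocation is 1:1 (Trial design section).

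**Step 1: reproduce the plan's own figures.**
- Standardised effect: d = difference / SD = 2.5 / 2.0 = 1.25.
- Power with n per arm is P(|T| > t*), where T is noncentral t with 2n − 2 degrees of freedom and noncentrality d × √(n/2), and t* is the 97.5% point of central t.
- Solving for 80% power at d = 1.25 gives n = 11.09, so 12 per arm, or 24 in total. With n = 12 the noncentrality is 1.25 × √6 = 3.06, t* = 2.074 (22 df), and power is 83.3%.
- Dropout: 24 / (1 − 0.20) = 30. Adding two gives 32.

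The chain 24, 30, 32 therefore reproduces, at d = 1.25.

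**Step 2: test 0.8 under each meaning.** Completers after 20% dropout from 32 are 32 × 0.8 = 25.6, or about 13 per arm. The table covers 12 per arm (the calculated minimum), 13 (expected completers) and 16 (no dropout).

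| Per arm | Power at 1.25 SD (2.5 min) | Effect detectable with 80% power | Power at 0.8 SD (1.6 min) |
|---|---|---|---|
| 12 | 83.3% | 1.20 SD (2.4 min) | 46.6% |
| 13 | 86.4% | 1.15 SD (2.3 min) | 49.9% |
| 16 | 92.8% | 1.02 SD (2.05 min) | 59.1% |

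- As the assumed effect, 0.8 is wrong: it is 1.25.
- As the effect detectable with 80% power, 0.8 is wrong at every plausible number per arm: the range is 1.20 to 1.02.
- A one-sided test, which the protocol does not use, would still leave 0.90 SD at 16 per arm.
- Detecting 0.8 SD with 80% power by the stated test needs n = 25.5, so 26 evaluable per arm.

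**Step 3: what 0.8 would require.** With SD 2.0 min it means a difference of 0.8 × 2.0 = 1.6 min. With a 2.5 min difference it means an SD of 2.5 / 0.8 = 3.125 min. Neither figure appears in the protocol. The inverted ratio 2.0 / 2.5 equals 0.8, which may be the source, but the document does not say so.

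**Step 4: allow for the planned baseline adjustment.** If the baseline-final correlation is ρ, the residual SD falls by the factor √(1 − ρ²), so the effective effect is 0.8 / √(1 − ρ²). The protocol gives no ρ; the values below are assumptions. The calculation takes 2.0 min as the unadjusted final-visit SD and ignores the degree of freedom spent on the covariate.

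| Assumed ρ | Effective effect | Power at 0.8 SD, 12 to 16 per arm |
|---|---|---|
| 0.3 | 0.8 / 0.954 = 0.84 | 50% to 63% |
| 0.5 | 0.8 / 0.866 = 0.92 | 58% to 72% |
| 0.7 | 0.8 / 0.714 = 1.12 | 75% to 87% |

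Reaching 80% power at 0.8 SD needs ρ of about 0.74 with 12 per arm, 0.72 with 13 and 0.62 with 16.

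**The case against.** The strongest reply is that the trial will not be analysed by an unadjusted t-test. The primary model adjusts for baseline, and under a high enough correlation 0.8 SD could be detectable with about 80% power. At an assumed ρ of 0.7 the effect detectable with 80% power is about 0.85 SD (12 per arm) to 0.73 SD (16 per arm). This stands as a limit on the point. A reader might infer from the second table column of power figures at 0.8 SD that the trial as designed has only 47% to 59% power there, or would miss such an effect about half the time. The documents do not support that: those figures belong to the planning t-test, and the power of the planned analysis is unknown without ρ. The reply does not rescue the sentence, however, because the protocol bases its calculation on the unadjusted test, states no correlation, and does not link 0.8 to the adjustment.

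A second reply is that nothing depends on the 0.8. It comes after the sample size has been fixed, and the true planning target is printed in the same paragraph. That also stands, and it limits the severity.

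A reader might also infer that a smaller effect than 2.5 min should be expected, because the Background cites a dose-dependent improvement at 30 and 90 billion CFU while this trial gives 5 billion daily. The protocol does not say which of those doses gave the 2.5 min and does not name this trial's strain. A ratio of CFU counts therefore shows nothing about the effect to expect here, and it forms no part of this point.

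**Conclusion.** The effect size of 0.8 is wrong as stated. The section's inputs give 1.25 SD, and its stated test detects 1.20 to 1.02 SD with 80% power across 12 to 16 per arm. These results use only figures in the protocol and the exact t-test calculation. Any statement about power at 0.8 SD under the baseline-adjusted model rests on an assumed correlation and ranges widely, from about 50% to 87% over the values tried.

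This does not show that the trial is too small for its stated target: 32 is adequate for 2.5 min with SD 2.0 min, with 83% power at 12 per arm and 93% if all 16 per arm complete. The point is a correction of one stated sensitivity figure, of modest severity.

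**What to change.** Delete the closing sentence of the Sample size section and put in its place:

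> The assumed effect is 1.25 SD (2.5 min / 2.0 min). By unadjusted two-sided t-test, with about 13 completers per arm, power is 86% for 2.5 min and 80% for about 2.3 min (1.15 SD); power for 0.8 SD (1.6 min) is about 50%. Baseline adjustment in the primary model may increase these figures.

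The words marking the figures as unadjusted should be kept, since without them the new text would misdescribe the planned analysis. The cost is one change of wording. Enrolment, procedures, endpoint and analysis stay as they are; the stated sensitivity simply becomes less favourable than 0.8 suggests.

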### Overall study timeline and procedures

This study will consist of four visits in total, spanning over a period of 9 weeks (Fig. 1). Eligible participants will begin a 2-week pre-baseline period followed by the 6-week intervention, and 1-week post-intervention follow-up during which information on activity, muscle soreness, supplement intake, gastrointestinal and immune health, and adverse events will be collected via daily and weekly questionnaires. The following procedures will be conducted at each of the four visits (detailed in Table 2):

**Fig. 1 Fig1:**
[figure not shown]
Study process diagram. AE, adverse events; BREQ-3, Behavioral Regulation in Exercise Questionnaire; BRPE, Borg Rating Perceived Exertion scale; sHEI, Short Healthy Eating Index; sIgA, secretory immunoglobulin A; VO_2_max, maximal rate of oxygen consumption

**Table 2 Tab2:**
[figure not shown]
Schedule of activities per visit

^a^A week before the randomization and the final visits

^b^Questionnaires are administered daily, starting 14 days before the randomization visit until 7 days after the end of the intervention (muscle soreness, cold-flu symptoms, stool frequency-consistency)

^c^Questionnaires are administered weekly starting 2 weeks before the Randomization visit until 1 week after the end of the intervention (GSRS, BSFS, DQLQ)

^d^Questionnaires are administered at baseline and final visits (sHEI, Fiber Screener, BREQ-3)

#### Visit 1: Informed consent

Potential participants will be asked to read the informed consent form and meet with a study coordinator in a semi-private area to complete the informed consent process.

#### Visit 2: V̇O_2_ max and activity tracking

Occurring 1 week into the 2-week pre-baseline, visit 2 will comprise V̇O_2_ max testing, pregnancy screening for females, and pre-intervention physical activity tracking. Before proceeding with visit 2 activities, female participants will complete a urine pregnancy test; those who test positive for pregnancy will not complete the visit and be withdrawn from the study.

##### V̇O_2_ max testing

During this pre-baseline visit, participants will complete a modified Bruce V̇O_2_ max treadmill test protocol (Table 3) to determine their aerobic fitness level, following procedures outlined by the ACSM [19]. Blood pressures, subjective ratings of muscle effort, and ratings of angina and dyspnea will be captured in the final minute of each 3-min stage. Muscle effort will be self-rated using the 11-point Borg Rating of Perceived Exertion Scale (BRPE), and angina and dyspnea will be self-rated using 5-point scales, where 0 = no symptom and 4 = worst imaginable symptom. Breath-by-breath measurement of gas exchange will be captured using open-circuit spirometry (Viasys Sensormedics®) at rest, during exercise, and during recovery. During this test, the speed and grade of the treadmill will be increased every 3 min until the participant reaches a maximal effort. The test starts with a very light walking warm-up (stages 1 and 2) and progresses to faster walking and then to running until the following criteria are achieved to indicate a true maximal effort. A maximal effort requires achievement of nonprotein respiratory quotient (RQ; V̇CO_2_/V̇O_2_) ≥ 1.1; minimum heart rate (HR) at 85% of age-predicted maximal HR (220 minus age); rating of 17 on the BRPE; and a plateau of minute-by-minute V̇O_2_ values. After the test is complete, the corresponding HR at which 85% V̇O_2_ max occurred is identified and used to set the running speed in the time-to-exhaustion treadmill endurance tests in the next visits. If there are no abnormal cardiopulmonary responses during the V̇O_2_ max test, as defined by the ACSM guidelines, the participant will be cleared to continue in the study.

**Table 3 Tab3:** Protocol for the modified Bruce V̇O_2_ max treadmill assessment to be completed at the pre-baseline visit

Stage	Time (min)	Speed (mph)	Grade (%)
Setup	−15:00–0:00		
20031	0:00–3:00	1.7	0
2	3:00–6:00	1.7	5
3	6:00–9:00	1.7	10
4	9:00–12:00	2.5	12
5	12:00–15:00	3.4	14
6	15:00–18:00	4.2	16
7	18:00–21:00	5	18
8	21:00–24:00	5.5	20
Recovery^a^	24:00–27:00	0	0

^a^For safety purposes participants will be asked to spend 15 min recovering during which heart rate and blood pressure will be measured but study measures will only be taken in the first 3 min

Any changes to physical activity levels could impact interpretation of the primary and secondary outcomes. Therefore, at the end of this visit, participants will receive an accelerometer activity tracker (SenseWear Armband Mini®) to record physical activity and sleeping patterns for 1 week (7 days) before randomization, with removal only while bathing/swimming. Depending on the speed, the percent error for step count in free living conditions for this device ranges from 0.9 to 13.7% [30].

#### Visit 3: Baseline treadmill endurance testing, biomarker sample collection, and randomization

The morning of the first treadmill endurance test, participants will be assessed for several physiological features that could influence running performance or physiological responses to exercise independent from the probiotic intervention. These include stress and immune biomarkers, changes in body composition, motivation to exercise, dietary patterns, and fiber intake. Participants will collect saliva via passive drool in a commercial test kit (SalivaBio Collection Aid, Salimetrics; State College, PA) within 45 min of waking up to assess stress-related biomarkers including cortisol, alpha-amylase, and salivary sIgA (all described in Table 1). Participants will also provide stool samples in a nucleic acid preservation tube (Norgen Biotek, Corp; Ontario, Canada). Participants will then consume a standardized breakfast. Participants will be told to eat the same light breakfast consisting of lower-fat foods (e.g., yogurt with fruit, half a bagel or toast with peanut butter, oatmeal with fruit) before visits 3 and 4. Food intake will be recorded at visit 3. Participants will be reminded of this intake before visit 4. Participants will bring their saliva and stool samples to the testing site and return the activity tracker armband. In the lab, height, weight, and body mass index (BMI) will be measured. Body composition (e.g., proportions of fat-free and fat mass, body density) will be assessed using a medical grade scale and air displacement plethysmography via BOD POD® (COSMED USA, Concord, CA). Participants will complete a series of questionnaires and perform the time-to-exhaustion endurance treadmill test (Fig. 2). The short Healthy Eating Index (sHEI) is administered to assess dietary intake [26]. The Fiber Screener is a free-access tool created by NutritionQuest® [27]. The Behavioral Regulation in Exercise Questionnaire (BREQ-3) is administered to assess the motivation for exercising [28, 31]. These questionnaires will be used to track changes in patterns of food consumption, dietary fiber, and mental state regarding exercise, all of which may influence the primary and secondary outcome measures.

**Fig. 2 Fig2:**
[figure not shown]
Treadmill endurance running test protocol for visits 3 (baseline) and 4 (final, 6 weeks post-intervention)

The treadmill endurance exercise test will be conducted at a level grade (Fig. 2). Participants will be asked to wear a HR monitor (Polar H10; Polar Inc; Dayton OH) throughout the test. The test consists of a 6-min warm-up period during which the speed of the treadmill will be increased until the participant achieves a HR of 85% of V̇O_2_ max and will continue at this speed until exhaustion or the participant asks to stop. Time-to-exhaustion is defined as meeting two out of three criteria: RQ ratio (VCO_2_/VO_2_) ≥ 1.1; HR reaches a minimum of 85% of age-predicted maximal HR (220 minus age); rating of 17 on the BRPE scale. Participants then remain seated for a recovery period where HR and blood pressure recover and are measured for safety before clearing participants to leave the testing area.

Throughout the test, HR, blood pressure, angina, dyspnea, and BRPE will be collected while finger prick blood samples will be used to measure glucose (Contour®Next EZ; blood glucose monitor; Parsippany, NJ) and lactate (Lactate Plus, Nova Biomedical; Waltham, MA) levels. These measurements will be collected at rest, 5 min into the treadmill test, then every 2–3 min until the participant reaches exhaustion, and once more 3 min after completion of the test.

After this visit, participants will begin their probiotic intervention and continue their daily and weekly questionnaires.

#### Visit 4: Post-intervention treadmill endurance testing

The procedures described for the endurance test, completion of questionnaires, salivary-stool biomarkers, and activity tracking with the armband described above for visit 3 will be repeated during this post-intervention visit. Participants will return any unused probiotic capsules for compliance calculation. Participants will complete daily and weekly questionnaires for an additional week after visit 4.

### Potential risks and discomforts

Potential risks may be associated with the probiotic or the treadmill testing***.*** Overall, probiotics do not pose a significant health risk and are generally regarded as safe. However, food allergy and gastrointestinal symptoms may occur in individuals who are allergic or intolerant to any of the ingredients in the probiotic. Treadmill testing (maximal or endurance testing) is associated with a minor risk of a fall or adverse cardiovascular complications. To minimize fall risks, spotters are present to support the participant should a fall occur, and a mirror is placed in front of the treadmill to help with spatial awareness. Although considered low risk, emergency equipment and a physician are available on site in the case of cardiac or vascular complications. If a participant experiences a complication believed to be related to the study, they will be withdrawn. Anticipated minor discomforts include finger tenderness during and after finger pricking from blood sampling. Lancet devices are used to minimize depth of puncture.

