### Probiotic intervention

The comparators were chosen to provide either active probiotic or inert placebo. The probiotic (5×10^9^ CFU/capsule) and corresponding placebo were provided by Lallemand Health Solutions Inc. This dosage was selected to determine probiotic efficacy in this athletic population. Placebo capsules contain the same excipients, namely ascorbic acid, magnesium stearate, and potato starch, without the probiotic. The probiotic and placebo capsules are sensorially identical (same smell, taste, and look) which allows for allocation concealment. Participants will receive all study capsules (probiotic or placebo) at the randomization visit and will be instructed to consume one capsule daily with a meal for 6 weeks. Criteria for discontinuing the intervention will be the occurrence of any clinical adverse event (AE) related to the intervention, laboratory abnormality, or other medical conditions (e.g., pregnancy) or situations such that continued participation in the study would not be in the best interest of the participant.

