### Primary and secondary outcomes

Primary and secondary outcomes are summarized in Table 1. The primary outcome measure is the difference in time-to-exhaustion during the endurance treadmill test (run at the HR corresponding to 85% of V̇O_2_ max) between the probiotic and placebo groups after a 6-week intervention. Changes will be adjusted for corresponding baseline time-to-exhaustion values. Longer time to exhaustion is a desired outcome for runners and offers a performance advantage in a competitive environment.

**Table 1 Tab1:** Descriptions of the study outcome measures

Outcome	Description
Primary	
Time-to-exhaustion during treadmill endurance run	During an endurance treadmill run performed at the heart rate (HR) corresponding to 85% maximal rate of oxygen consumption (V̇O_2_max), the participant will run until voluntary time to exhaustion (reflected by meeting 2 out of 3 criteria: respiratory quotient ratio (VCO_2_/VO_2_) ≥ 1.1; HR reaches a minimum of 85% of age-predicted maximal HR (220 minus age); rating of 17 on the 6 to 20 point Borg Rating of Perceived Exertion scale (BRPE).
Secondary	
Blood chemistries	Capillary blood samples will be collected before, during, and after the treadmill endurance test to determine concentrations of glucose and lactate. These metabolites will be quantified using commercial, handheld colorimetric devices (ContourNext EZ glucose meter, LactatePlus lactate meter).
Body composition	This variable will be assessed using the scale (to assess weight) and BOD POD®, a body composition measuring device that measures fat mass and lean muscle mass. Coefficients of variation are 12%, and ICC are 0.9 [20].
Borg Rating of Perceived Exertion Scale (BRPE):	Exertion is a subjective estimate of exercising intensity. This self-reported instrument assesses effort and fatigue due to physical work [21]. Ratings range from 6=no muscle effort to 20=maximal muscle effort possible, cannot work any harder.
Bristol Stool Scale (BSFS):	Is a 7-point, self-rated scale of changes in stool form (hardness, shape, water content) that corresponds to intestinal transit time (*r*=−0.65) [22]. This tool is being used to monitor responses to the intervention and is supported for use in gastrointestinal research.

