### Adverse events, seriousness, and reporting

An adverse event (AE) and serious AE will be determined and addressed per the International Council for Harmonisation of Technical Requirements for Pharmaceuticals for Human Use Guidelines for Good Clinical Practice [32].

All AEs and serious AEs will be captured on an adverse events report log. Serious AEs will be reported within 24 h of knowledge of the event to the sponsor and the IRB, commensurate with the determination of possible relation to the intervention. A written report will be submitted to the sponsor and IRB within 7 days of the initial reporting. Changes in the severity of an AE will be documented to allow an assessment of the duration of the event at each level of severity to be performed. AEs characterized as intermittent will require documentation of onset and duration of each episode. Study participants will be followed for 1 week after the final study supplement is consumed. If an AE occurs, which in the judgment of the study sponsor and investigators was directly caused by the study supplement or protocol activities, the study sponsor will pay for medical care as defined in the informed consent form.

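### The rule that a study-related complication leads to withdrawal can be read to remove a participant with a capsule reaction from the study, and with them the only post-baseline primary value

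*Protocol article*

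**What the plan says.** Four parts of the Protocol article bear on this point.

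- **Potential risks and discomforts.** The paragraph opens "Potential risks may be associated with the probiotic or the treadmill testing". It names allergy and gastrointestinal symptoms as possible capsule reactions, moves on to falls and cardiovascular events on the treadmill, and then gives the rule: "If a participant experiences a complication believed to be related to the study, they will be withdrawn".
- **Probiotic intervention.** A different consequence is attached to a related adverse event: "Criteria for discontinuing the intervention will be the occurrence of any clinical adverse event (AE) related to the intervention". The same sentence goes on to situations in which staying in the study would not serve the participant, so it mixes stopping the capsules with leaving the study.
- **Other uses of the word.** Under Visit 2, withdrawal means study exit: "those who test positive for pregnancy will not complete the visit and be withdrawn from the study". Under Eligibility criteria, a participant who starts antibiotics is not withdrawn and goes on taking the supplement.
- **Primary outcome and analysis.** The primary comparison is made "between the probiotic and placebo groups after a 6-week intervention". The endurance test is run at visit 3, before the first capsule, and "will be repeated during this post-intervention visit" at visit 4. Statistical methods plans intent-to-treat and per-protocol analyses, with no imputation where an outcome is measured only once.

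**The concern.** A capsule reaction can occur only after visit 3, because the capsules start then. If the participant is taken out of the study at that point, there is no visit 4 run. The intent-to-treat linear model has nothing to use for that person, so in practice the analysis is of completers.

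The loss may also depend on treatment, since it is triggered by a reaction attributed to the study product. Gastrointestinal symptoms are both a listed capsule risk and a secondary outcome, so the people removed could be informative there too. An analysis plan cannot recover a run that was never done, so the remedy lies in trial conduct.

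**Working it through.** **Which events can cause the loss**

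| Event | When it can occur | Effect on the primary value if withdrawal means study exit |
|---|---|---|
| Treadmill complication, visit 2 or 3 | Before the first capsule | Not caused by treatment |
| Treadmill complication, visit 4 | During or after the primary test | No loss between first capsule and test |
| Capsule reaction | Between visits 3 and 4 | The only post-baseline value is lost, possibly because of treatment |

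Only the third row matters, and it needs both the wider scope and the study-exit reading.

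**Inputs.** From Sample size: difference 2.5 min, SD 2.0 min, two-sided alpha 0.05, 12 per arm for 80% power, 20% dropout, 16 per arm randomised. Assumed, because the article gives no figure: one participant lost in one arm, and D (mean of the missing minus mean of the completers in that arm) between -2 and +2 min, which is one planning SD either way.

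**The plan's own figure.** Exact two-sample t power is 0.796 at 11 per arm and 0.833 at 12 per arm, so 12 is the smallest size per arm that reaches 80%. Then 24 / (1 - 0.20) = 30, and two more give 32. The stated sample size is reproduced.

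**Standard error of the difference.**
- 16 v 16: 2.0 × √(1/16 + 1/16) = 0.707 min.
- 15 v 16: 2.0 × √(1/15 + 1/16) = 0.719 min.

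**Bias from one loss.** The full-arm mean is (15 × completer mean + missing value)/16, which equals the completer mean + D/16. Using completers alone therefore shifts that arm's mean by -D/16.
- D = ±2 min: 2/16 = 0.125 min in size; 0.125/2.5 = 5% of the target; 0.125/0.707 = 18% of the standard error.
- D = ±1 min: 1/16 = 0.0625 min; 0.0625/2.5 = 2.5% of the target.

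**Power for 2.5 min.** 0.928 at 16 v 16 and 0.919 at 15 v 16.

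**Price of keeping the participant.** If one of 16 stops the probiotic and loses the whole effect, the expected difference falls by 2.5/16 = 0.156 min to 2.344 min (6%). Power at 16 v 16 is then 0.894.

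**The case against.** The strongest reply is that the sentence concerns the treadmill only. Elsewhere in that paragraph the word complication is used for cardiovascular events, while capsule reactions are called allergy and symptoms, and the sentence comes straight after the treadmill safety measures. Capsule reactions would then fall under Probiotic intervention, where the consequence is to stop the intervention, and the two sections would cover different events. This reading is plausible and, as the table shows, it removes the harm. It is not the only reading: the rule speaks of relation to the study, and the paragraph opens with both sources of risk.

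A second reply is that the article condenses a full protocol that is not shown. That stands for one part. The article's silence on whether someone who stops the capsules still attends visit 4 is not a fault by itself. The point rests on the mandatory rule that is printed.

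A third reply is that the figures do not favour the change: dilution of 0.156 min against a bias of at most 0.125 min, and power of 0.894 against 0.919. The arithmetic is right, but the two quantities differ in kind. Dilution belongs to the effect that an intent-to-treat analysis sets out to estimate. Bias from selective loss does not, and its direction is unknown.

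Stronger readings that a reader might infer are not supported:

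- **That the protocol plainly orders study exit after a capsule reaction.** The rule names no object. The Visit 2 wording fits study exit, and the antibiotic wording is compatible with it, but neither proves it.
- **That the follow-up period cancels visit 4.** The statement "Study participants will be followed for 1 week after the final study supplement is consumed" is a general adverse-event follow-up and ends no scheduled visit.
- **That the reference to an event that "was directly caused by the study supplement or protocol activities" shows that withdrawal covers both causes.** That sentence is about who pays for medical care.

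**Conclusion.** The point holds in conditional form, as something to consider. The printed rule is mandatory, has no severity threshold, and can plausibly be applied to a capsule reaction as study exit. If so applied, it removes the single post-baseline primary value for a possibly treatment-related reason.

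The size is small and uncertain: at most 0.125 min for one loss in 16, given an assumed difference of no more than 2 min. The article gives neither the number likely to be affected nor how they would differ, and more losses or larger differences would scale the bias in proportion. Power is not the concern. The documents do not support calling the primary analysis invalid. Confidence is medium, because the treadmill-only reading cannot be excluded.

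**What to change.** Amend the Probiotic intervention and Potential risks and discomforts sections to say:

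- A supplement-related complication stops the supplement only.
- Unless consent is withdrawn, the participant keeps the scheduled daily and weekly questionnaires and visit 4.
- The visit 4 run is done only where the investigator judges it safe.
- The participant is analysed in the randomised arm.
- Treadmill safety stops are unchanged.

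The follow-up sentence in the adverse-events section needs no change.

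The cost is a short amendment and a little extra follow-up for a few people, using assessments already scheduled. The article reports that enrolment is still open, so the change can still protect data. The statistical cost is the slight dilution shown above, which leaves power above the planned 80%. A primary value may still be missing where the run is judged unsafe.
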